#### **4.1 Number of subjects**

Data will be collected from an anticipated sample of up to 4,000 Mexican healthcare providers who work in a participating healthcare system within a participating Mexican State (Campeche, Coahuila, Guanajuato, Jalisco, Nuevo Leon, Oaxaca, Queretaro, or Sonora).

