## **7 STUDY PROCEDURES AND VISITS**

### **7.1 Randomization**

Using stratified random permuted blocks of 4, with Mexican State and the tier of healthcare facility as the strata, participants will be randomly assigned 1:1 to either the ISTH or wait-list control. The randomization list will be entered into REDCap and participants will be auto-assigned based on strata via REDCap's assignment features (i.e., no experimenter involvement).

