### 8.4 STATISTICAL ANALYSIS PLAN

See <https://osf.io/9g58j> for preregistration of statistical plan, hypotheses and outcomes.

Primary and secondary outcomes will be analyzed using linear mixed effects models with time nested within participant. All randomized participants will be included (i.e., intention-to-treat analyses). Maximum likelihood estimation will be used for missing data. To help determine the best fit for modeling change over time, we will plot outcomes over time by group using loess regression. We will then quantitatively compare the Akaike Information Criterion (AIC) and Bayesian Information Criterion (BIC) of candidate models of linear change, loglinear change, polynomial change, and piecewise linear change in which change over the intervention period is modeled separately from change over follow-up. Primary effects of interest are groupXtime interactions from pre- to post, pre- to 3-month follow-up, and pre- to six month follow-up. We will control for gender and age. Models with and without social desirable responding will be compared and the best fitting model will be used.

Covariates may be centered to aid in model interpretation. Statistical significance will be set at a two-tailed alpha of  $p < 0.05$ , false discovery rate corrected for the 9 inferential tests at post-test (2 primary, 7 secondary outcomes) and the three inferential tests at 6-month follow-up. In addition to statistical significance, magnitude of differences will be estimated using standardized mean differences on continuous outcomes and Odds Ratios on binary outcomes.

Before hypothesis testing, we will use the "careless" package in R to check for patterns of aberrant responding on the survey items. Should evidence for inattentive responding be observed, we will report results with and without affected data removed. Given the expected sample size, we do not expect outliers or high leverage points to be observed but we will use simulation methods to check models for these points. Should high influence points be observed, we will report models with and without them.

Should evidence for data not missing at random be observed (e.g., differential attrition between groups, inability to predict missingness based on observed variables) we will conduct pattern-mixture modeling.

We will examine moderation of intervention effects on primary and secondary outcomes by participants gender, age, employment type and location.

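### The covariates stated for the mixed models leave out State and facility tier, the factors that stratify randomisation; the loss of precision is small and conservative

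*Protocol*

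**What the plan says.** Randomisation (Protocol, 7.1): "Using stratified random permuted blocks of 4, with Mexican State and the tier of healthcare facility as the strata", and "participants will be randomly assigned 1:1 to either the ISTH or wait-list control". Section 4.1 lists eight States ("Campeche, Coahuila, Guanajuato, Jalisco, Nuevo Leon, Oaxaca, Queretaro, or Sonora"). The number of facility tiers is not given.

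Analysis (Protocol, 8.4): primary and secondary outcomes go into "linear mixed effects models with time nested within participant", fitted by maximum likelihood to all randomised participants. The estimand is stated: "Primary effects of interest are groupXtime interactions from pre- to post, pre- to 3-month follow-up, and pre- to six month follow-up". The covariate sentence is "We will control for gender and age". Socially desirable responding enters if it improves model fit. Geography returns once, as an effect modifier: "We will examine moderation of intervention effects on primary and secondary outcomes by participants gender, age, employment type and location". Facility tier is not mentioned in 8.4. The section opens by pointing to an outside preregistration for the statistical plan, which is not at hand.

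**The concern.** The two factors that restrict the randomisation are not among the covariates named for the models, and the two covariates that are named played no part in the randomisation. Blocking within strata removes between-stratum variation from the sampling distribution of the arm difference. A model without the strata leaves whatever part of that variation bears on the tested contrast in its error term, so its standard error is larger than the design implies.

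This is a stated covariate set, not silence that a later plan would be expected to fill. What is at stake is precision and agreement between analysis and design. The validity of the arm comparison is not in question.

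**Working it through.** **The plan's own figures.** The point disputes none of them. The biomarker sample size of 468 (section 8.2) is roughly reproduced by the usual within-between interaction test: f = d/2 = 0.075, three occasions, r = 0.60, alpha 0.005, power 0.90, noncentrality f² × N × 3 / (1 − r). This gives N = 463, and power at 468 is 0.905. The calculation contains no stratum term.

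**Inputs from the protocol.** N = 4,000 with 1:1 allocation, r = 0.50 between assessments, alpha 0.006, power 0.80 (section 8.2); eight States (section 4.1).

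**Assumed, because the protocol does not give them.** State and tier explain 2–10% of variance in outcome level. Stratum-specific change has a variance of 0–3% of outcome variance. There are two or three tiers. Outcome SD is 1.

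**Step 1: level differences, complete data.** The variance of a pre-to-post change is 2(1 − r) = 2 × 0.50 = 1. The standard error of the difference in change between arms is √(1 × 4/4,000) = 0.0316. A constant State or tier effect is present at both time points and drops out of the change, so this value is the same with or without stratum main effects.

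Simulated random-intercept models agree (two time points, intraclass correlation 0.5, 1,000 participants, permuted blocks of four in 24 assumed strata, 15 replicates). The ratio of the group-by-time standard error with strata to that without is 1.0000 when strata explain 2%, 5% or 10% of variance.

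**Step 2: level differences, 30% missing at follow-up.** Participants with one measurement contribute between-person information, so a little can be gained. The simulated ratios are 0.9988, 0.9977 and 0.9952 for 2%, 5% and 10%. The unadjusted standard error is therefore about 0.1–0.5% too wide.

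**Step 3: stratum-specific change.** If strata differ in change with variance v, the unadjusted standard error is √((1 + v) × 4/4,000).

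| v | Unadjusted SE | Adjusted / unadjusted | Detectable change, unadjusted (SD) | Actual type I error at nominal 5% |
|---|---|---|---|---|
| 0 | 0.0316 | 1.000 | 0.1135 | 5.0% |
| 0.01 | 0.0318 | 0.995 | 0.1141 | 4.9% |
| 0.03 | 0.0321 | 0.985 | 0.1152 | 4.7% |

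The detectable change is (2.748 + 0.842) × SE, for a single pre-to-post contrast. It is not on the same footing as the detectable effects in section 8.2 and is shown only for the relative movement. Actual type I error is 2 × [1 − Φ(1.96 × √(1 + v))].

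The values in this table are analytic. In the simulation, adding stratum-by-time terms gave ratios of about 0.988–0.989 with complete data even when no true stratum-by-time effect existed. That comes from maximum likelihood variance estimation with many parameters at 1,000 participants and is not a real gain.

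**Step 4: cost in parameters.** State takes 8 − 1 = 7 and tier takes 1 or 2, so 8–9 for the main effects and 8–9 more for each time term.

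**The case against.** The strongest reply is that the preregistration may already list the strata. Section 8.4 defers to it and does not say that gender and age are the whole list. That stands as a reason to make the request conditional. It does not remove the point, because the protocol chose to state covariates and the stated ones leave out the randomisation factors.

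The second reply concerns size, and it stands in full. A reader might infer that the standard errors are materially too wide. For a comparison of post-treatment scores alone, strata explaining 2–10% of variance would inflate the standard error by 1/√(1 − R²), that is 1.0–5.4%. The tested effects here are group-by-time interactions with repeated measures within participant, so that formula would apply only if State and tier explained 2–10% of the variance in change. Nothing in the protocol suggests this.

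A reader might also infer that the benefit of stratification is lost. It is not: balance of the arms across State and tier comes from the randomisation and holds whatever covariates are used.

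The planned moderation by location does not answer the point. It is a separate analysis, and it leaves out facility tier.

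**Conclusion.** The mismatch is real: randomisation is stratified by State and facility tier, and the covariates stated for the models are gender and age. Its effect on the stated group-by-time effects is minor. The standard error is about 0.5–1.5% too wide if stratum-specific change is 1–3% of outcome variance, about 0.1–0.5% too wide from level differences if 30% are missing at follow-up, and unchanged if neither applies. These shares are assumptions.

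The direction is conservative. The omission does not of itself bias the arm comparison or raise the type I error, and it is unlikely to change a conclusion at up to 4,000 participants. The case for acting is that the analysis should follow the randomisation and that doing so is nearly free.

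**What to change.** Replace the covariate sentence in section 8.4 with: *We will control for State and facility tier (the stratification factors, as recorded at randomisation), each with its interaction with the chosen time terms, plus gender and age.* If the preregistered plan already does this, say so in section 8.4 instead.

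The interactions matter most, since main effects alone gain nothing for these contrasts with complete data. The wording refers to the chosen time terms because section 8.4 selects the form of change (linear, loglinear, polynomial or piecewise) by AIC and BIC, so visit may not be categorical.

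The cost is one sentence, no new data, and about 8–9 degrees of freedom per time term in addition to the main effects, negligible at up to 4,000 participants. In the 510-participant biomarker subsample the cost is still small. Section 8.2 says only that 255 are selected at random from each group, so balance by State and tier is not described there, and the same terms would serve as ordinary covariate adjustment.

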#### **6.1.2 Secondary Outcomes**

Secondary Outcomes consist of: the Healthy Minds Index (17-items), a measure of four components of well-being – awareness, connection insight and purpose; Gratitude Questionnaire 6 (6-items); and the Maslach Burnout Inventory Emotional Exhaustion and Personal Accomplishment subscales (15-items).

Administrative records. We will receive prior, current and next year employment records on participants, including, number and reasons for absences and type of employment. Biomarkers - Dried blood spot substudy: CRP, IL-6, IL-10, TNFalpha.

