### 8.2 SAMPLE SIZE AND POWER ANALYSES

Our target sample size was informed in part by our agreements with State Ministers of Health, which requested a minimum number of participants from each participating state. Because of the large, planned sample size (up to 4,000), we conducted two power analyses. First, we conducted a sensitivity power analysis to determine the smallest detectable effect based on the lower bound of the expected intention-to-treat sample of 4,000. To ensure our power estimates were conservative, we based power calculations off of the Bonferroni corrected two-tailed p-value assuming that all primary and secondary outcomes in the parent trial share the same family-wise error 0.05 error rate. We plan to test a total of 9 primary and secondary outcomes for a Bonferroni corrected error rate of 0.006. For measures collected at all 10 assessments points, we assume:

- 0.80 power
- A correlation of  $r = .50$  between the same measure at different assessments
- Error rate of 0.006

Under the above conditions, we will be able to detect a significant group by time interaction effect of Cohen's  $d \geq 0.04$ . For measures assessed at five of the timepoints, assuming the same conditions listed above, we will be able to detect between group effects of Cohen's  $d \geq 0.05$ .

We conducted a second power analysis to determine the size of the randomly selected biomarker and patient satisfaction report subsample required to detect a pre- to post-test change of  $d \geq 0.15$ . We selected  $d \geq 0.15$  as our expected effect size because, in two meta-analyses on the topic of mindfulness-based interventions effects on inflammation,  $d \geq 0.15$  was the smallest observed average effect size on the cytokines we will assay. We assume:

- 0.90 power
- A correlation of  $r = .60$  between the same measure at different assessments
- Error rate of 0.005

In order to detect a statistically significant group by time interaction effect of Cohen's  $d \geq 0.15$  on our measures of peripheral inflammation, we will require a subsample of 468 participants. Assuming 10% of selected participants do not provide a pre-test sample, we plan to randomly select 255 participants from each group (510 total) to participate in biomarker data collection.

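### Week-24 contrasts, declared primary effects of interest, sit in no false-discovery-rate family, and the counts of 9 and three do not identify which tests are corrected

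*Protocol*

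**What the plan says.** Section 8.4 of the protocol names the contrasts that matter: "Primary effects of interest are groupXtime interactions from pre- to post, pre- to 3-month follow-up, and pre- to six month follow-up". Section 4 equates post-intervention with week 12, so the 3-month and 6-month follow-ups are weeks 24 and 36.

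The same section sets a two-sided 0.05 level, "false discovery rate corrected for the 9 inferential tests at post-test (2 primary, 7 secondary outcomes) and the three inferential tests at 6-month follow-up". It does not mention the 3-month tests, list the members of either group, name the false-discovery-rate procedure, or say whether 9 and three are two families or one of twelve. No section says whether one or both co-primaries must succeed.

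Section 6.1.2 lists as secondary:
- the Healthy Minds Index, described as covering four components;
- the six-item gratitude questionnaire;
- the "Maslach Burnout Inventory Emotional Exhaustion and Personal Accomplishment subscales (15-items";
- employment records;
- "Biomarkers - Dried blood spot substudy: CRP, IL-6, IL-10, TNFalpha".

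Section 7.2 schedules the distress scales, WHO-5, the burnout inventory and blood spots at week 24. At week 36 it schedules the distress scales, WHO-5 and the burnout inventory.

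Section 8.2 bases power on 9 tests at a Bonferroni level of 0.006, "assuming that all primary and secondary outcomes in the parent trial share the same family-wise error 0.05 error rate". It sizes the biomarker substudy separately, at 0.005.

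**The concern.** A contrast that the plan calls primary has no multiplicity control, while the contrasts before and after it do. Followed literally, a week-24 effect could be claimed on a nominal p-value below 0.05 and reported beside corrected results as if it carried the same weight.

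A correction is also only defined once its members are known. If two analysts can apply the same sentence to different sets of tests, the adjusted p-values are not fixed in advance. Whether the four biomarkers are corrected at all then depends on the reading.

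Finally, when co-primaries and secondaries share one false-discovery-rate family, the threshold that a co-primary must meet depends on how many secondaries are significant.

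**Working it through.** **The plan's own figure.** 0.05 / 9 = 0.00556, which rounds to the stated 0.006. Section 8.2 therefore agrees with the 9 in Section 8.4.

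**Week 24.** Distress is one composite, so there are two co-primary tests. Burnout adds one or two more, giving three or four survey tests. With k independent tests at an unadjusted 0.05, the chance of at least one false positive is 1 − 0.95^k:

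| Tests at week 24 | k | Chance of at least one false positive |
|---|---|---|
| Co-primaries only | 2 | 1 − 0.9025 = 9.8% |
| Plus burnout as one test | 3 | 1 − 0.8574 = 14.3% |
| Plus both burnout subscales | 4 | 1 − 0.8145 = 18.5% |

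These scales are answered by the same people and are probably positively correlated, which moves each figure down towards 5%.

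**Which tests make up 9 and three.** The post-test total is 2 primaries plus Healthy Minds, gratitude, burnout and biomarkers. The week-36 total is 2 primaries plus burnout, because no other primary or secondary outcome is scheduled then.

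| Reading | Post-test | Week 36 | What it leaves unresolved |
|---|---|---|---|
| A: four Healthy Minds components, gratitude, two burnout subscales | 2 + 4 + 1 + 2 = 9 | 2 + 2 = 4 | Gives 4, not three; the biomarkers are in no family |
| B: one Healthy Minds score, gratitude, burnout once, four biomarkers | 2 + 1 + 1 + 1 + 4 = 9 | 2 + 1 = 3 | Treats two listed subscales as one test; puts in the nine the biomarkers that Section 8.2 powers separately |
| Every scale and biomarker, Healthy Minds as one score | 2 + 1 + 1 + 2 + 4 = 10 | 4 | Matches neither count |
| Every scale and biomarker, four components | 2 + 4 + 1 + 2 + 4 = 13 | 4 | Matches neither count |

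Other combinations also reach the stated counts. For example, four components plus a total score, gratitude and burnout once gives 2 + 5 + 1 + 1 = 9 and 2 + 1 = 3. Among the scheduled outcomes, three at week 36 always requires burnout to be counted once.

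**Pooling the co-primaries.** The protocol names no procedure, so Benjamini-Hochberg at 0.05 is assumed. Take the worst case: both co-primaries null, all seven secondaries truly different and all rejected. The smaller co-primary p-value then ranks eighth of nine and is compared with 0.05 × 8/9 = 0.0444; both are rejected if both are at or below 0.05. With independent tests,

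P(at least one) = 1 − (1 − 0.0444)² + (0.05 − 0.0444)² = 0.0869 + 0.00003 ≈ 8.7%.

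Simulation (1,000,000 runs) gives:

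| Secondaries truly different | Correlation 0 | 0.5 | 0.7 |
|---|---|---|---|
| 7 | 8.7% | 8.1% | 7.5% |
| 3 | 4.5% | 4.5% | 4.4% |
| 0 | 1.2% | 1.7% | 2.1% |

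With the two co-primaries as their own Benjamini-Hochberg family (for two tests, the same rule as Hochberg), the simulated error is 4.6% to 5.1%.

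**The case against.** **The counts.** A reader might infer that 9 and three fit no reading of the outcome list. That is wrong: reading B gives both, and Section 7.2 marks exactly three primary or secondary rows at week 36. A reader might also count 11 or 14 post-test tests by adding absences. Section 6.1.2, however, describes records that run into the next year, and the schedule has no administrative outcome at week 12. What stands is that the readings conflict and the protocol does not choose between them.

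**Family-wise error.** Section 8.2 could be read as promising family-wise control that Section 8.4 then withdraws. It is not a promise: the Bonferroni level is introduced to keep the power estimates conservative, and Section 8.4 promises only false-discovery-rate control.

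**Pooling.** The 8.7% needs every secondary to be truly different, both co-primaries null, and success on either to count. With three or fewer truly different secondaries, the simulated error is below 5%. If both co-primaries were required, the inflation would not arise: the largest error, with one co-primary and all secondaries real, is 0.05 × 9/9 = 5%. To say that pooling loses control would therefore be too strong.

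**Biomarkers at week 24.** Adding four biomarkers at 0.05 would give 1 − 0.95^8 = 34%. The only biomarker error rate in the protocol is 0.005; with that rate the figure is 1 − 0.95^4 × 0.995^4 = 20%. The 34% is not supported.

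**What lies elsewhere.** The preregistration cited in Section 8.4 may list the members, and it is not at hand. Version 1.1, dated 12.20.2024, adjusted the number of tests. That is after week 36 for someone enrolled at the planned close of recruitment on May 21, 2023 (252 days later is January 28, 2024). A reader might infer that the tests were chosen with results in view. The protocol does not say when the data were analysed, so this cannot be concluded. The week-24 gap does not depend on the unseen plan: one paragraph names three primary contrasts and the next states corrections for two.

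**Conclusion.** The week-24 gap is a plain mismatch within Section 8.4. Its size is 9.8% for the two co-primaries and up to 18.5% for four survey tests. Both figures assume independence and an unadjusted 0.05 level; that level is inferred because the section is silent on week 24.

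The counts are attainable but do not define the families. The reading that best fits the parent-trial wording of Section 8.2 gives 4 tests at week 36 and leaves the biomarkers uncorrected. The reading that gives both counts merges two listed subscales.

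The pooling point is conditional. One shared family does not guarantee family-wise control over the co-primaries. The error is about 8.7% at worst under Benjamini-Hochberg with either co-primary sufficient, and below 5% when few secondaries have real effects.

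**What to change.** 1. Add a week-24 false-discovery-rate family covering the outcomes measured then: distress, WHO-5 and burnout, with the biomarkers either included or explicitly assigned elsewhere.
2. List the members of the post-test and week-36 families by name, so that the counts agree with Sections 6.1.2 and 7.2. Week 36 has four tests if both burnout subscales are tested. State whether Healthy Minds contributes one score or four components, where the substudy biomarkers are corrected, which procedure is used, and whether the time points form separate families.
3. Preferably, test the two co-primaries at week 12 as their own family, for example by Holm or Hochberg at 0.05. Otherwise, state whether either or both must succeed.

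The cost is wording, plus slightly stricter thresholds at follow-up and for the secondaries. The third change need not cost the co-primaries power. In the pooled family, a co-primary that is the only significant result needs p ≤ 0.05/9 = 0.0056; in a family of two it needs p ≤ 0.05/2 = 0.025.

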## **9 DATA MANAGMENT**

Data will be collected for research purposes only. Data will be stored and handled according to agreements with State Minister's of Health, supervising review board in Mexico, and policies of the University of Wisconsin Madison.

### **9.1.1 DATA MONITORING PROCEDURES**

The Mexico based implementation team and US based research team will meet weekly throughout the project to ensure data quality and proper data management and storage.

## **10 SAFETY AND ADVERSE EVENTS**

### **10.1 DEFINITIONS**

**Adverse Event (AE):** An AE is as any untoward medical occurrence in a participant and which does not necessarily have a causal relationship with a study treatment.

**Serious Adverse Event (SAE):** A SAE is any AE that:

- Results in death;
- Is life threatening, or places the participant at immediate risk of death from the event as it occurred;
- Requires or prolongs hospitalization;
- Causes persistent or significant disability or incapacity;
- Results in congenital anomalies or birth defects;
- Is another condition, which the investigators judge to represent significant hazards.

**Unanticipated Problem:** any incident, experience, or outcome that meets all of the following criteria:

- Unexpected, in terms of nature, severity, or frequency, given the research procedures that are described and the characteristics of the study population;
- Related or possibly related to participation in the research;
- Suggests that the research places participants or others at a greater risk of harm (including physical, psychological, economic, or social harm) than was previously known or recognized.

**Adverse Event Reporting Period:** The period from the initiation of study procedures to the end of the study treatment follow-up.

**Preexisting Condition:** A preexisting condition is one that is present at the time of providing the consent for the study. A preexisting condition is considered an adverse event if the frequency, intensity, or the character of the condition worsens during the study period.

